#### Exclusion criteria

Formula feedingSmall for gestational age (birth weight < 3rd percentile)Presence of congenital abnormalities, which increase the risk of NECNECWithdrawal of feeding > 7 daysSepsisDeath

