#### Secondary outcomes

Growth (weight, length, head circumference) will be assessed at discharge and at 4 months of corrected age.Body composition (percentage of body fat, fat mass, fat-free mass) will be measured at discharge and at 4 months corrected age by air plethysmography (PeaPod).^1^Neurodevelopmental outcome:
12 months corrected age: BSID-III (Bayley Scale of Development Third Edition); the following stratification of index composite scores will be used in our study:< 70 (> 2 SD below the mean)—severe impairment70–84 (> 1 SD below the mean)—mild impairment≥ 85—normal development3.5 years of corrected age: BSID and WPSSI-IV (Wechsler Preschool and Primary Scale of Intelligence, Fourth Edition IV).Behavioural problems: parental assessment by CBCL (Child Behaviour Check List) at 3.5 years corrected age.Feeding tolerance under whole period of fortification.Morbidity: incidence of necrotizing enterocolitis (NEC), retinopathy of prematurity (ROP) and bronchopulmonary dysplasia (BPD), intraventricular haemorrhage (IVH), periventricular leukomalacia (PVL), sepsis, and pneumonia. Definitions provided below.

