##### Definitions

Feeding tolerance: defined as haemorrhagic residuals or vomiting bile until pathological causes are ruled out (intestinal obstruction or ileus) [17]. Gastric residuals and abdominal girth will not be checked routinely. Isolated green or yellow residuals will be considered unimportant.NEC (necrotizing enterocolitis): stage II or III. Stage II requires clinical manifestations of distended abdomen and radiological verification (intramural and/or portal gas). Stage III requires findings like in stage II and more severe clinical symptoms (shock, need for respirator). In surgery verified cases, no radiological verification is needed [18].ROP (retinopathy of prematurity): stages I to V, diagnosed by an ophthalmologist according to international criteria [19].BPD (bronchopulmonary dysplasia): need for oxygen, continuous positive airway pressure (CPAP), or mechanical ventilation at 36 + 0 weeks gestational age [20].IVH (intraventricular haemorrhage) [21].PVL [21].Early- and late-onset sepsis defined as a positive blood or cerebral fluid culture at less or more than 72 h of age, respectively [22].

Feeding tolerance has been chosen as an efficacy and harm outcome in order to evaluate whether TEN may impact milk absorption in the intervention group. Exclusive breastfeeding decreases the risk of NEC; however, the impact of TEN on the risk of developing NEC has not yet been studied. Blood culture confirmed early-onset sepsis (EOS) is a known risk factor for delayed implementation of EN and can impact the risk of late-onset sepsis (LOS). Diagnosis of EOS and LOS can be associated with intermitted withdrawal of enteral nutrition, BPD, IVH, and PVL which are markers of neonatal morbidity; hence, we decided to include them in our analysis.

Time schedule of enrolment, interventions (including any run-ins and washouts), assessments, and visits for participants is presented in Table 2.

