#### Implementation {16c}

A member [a physician not involved in the patients care] of the research team will prescribe the allocated fortification on the patient’s drug chart. Milk fortification is routinely done twice a day (at 8 am and at 8 pm) for each following 12-h nursing shift (Fig. 1). For the purpose of the study, TF will be integrated in this schedule and performed by experienced registered nurses (RNs). The intervention will be performed by a RN blinded to treatment allocation. Patient’s data along with the result of the allocation will be sent to the statistical team. The randomization list will remain with the statistical team for the whole duration of the study.

All randomized infants who are prematurely discontinued from study will be considered *off study intervention/on study* and will follow the same schedule of events as those infants who continue study treatment. All of these infants will be followed through 36 months as scheduled. Once an infant is enrolled or randomized, the study site will make every reasonable effort to follow the infant for the entire study period. Participants may withdraw from the study for any reason at any time.

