### Statistical methods

#### Statistical methods for primary and secondary outcomes {20a}

Baseline characteristics will be presented for all included neonates in intention-to-treat and per-protocol analysis sets, by treatment group. Dichotomous variables will be presented as frequencies, categorical variables as median and interquartile ranges, and continuous variables as mean and standard deviations, along with 95% CI. In cases of missing data, i.e. due to adverse events or dropouts, in follow-up analysis, a weighted average taking account of changes in the gender ratio will be applied. Continuous variables will be tested against normality of distribution and the equality of variances between groups. For continuous variables distributed normally, the differences in means will be tested using *t* test; for continuous variables not distributed normally and for categorical variables between groups, comparison will be performed using the Mann-Whitney *U* test. The primary outcome will be assessed with one-tailed unpaired two-sample *t* test for noninferiority. Secondary and safety outcomes will be tested for two-sided superiority. Proportions of dichotomous variables will be tested using chi-square or Fisher’s exact test, whichever appropriate. In addition, the risk ratio (RR), the odds ratio (OR), and the number needed to treat will be assessed. For secondary outcomes, the difference will be considered significant when *p* value calculated in statistical tests will be < 0.05 or when the 95% CI for the mean difference will not include 0, or 1 in case of RR or OR.

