#### Methods in analysis to handle protocol non-adherence and any statistical methods to handle missing data {20c}

Linear regression will be used to fill missing data.

In addition, a sensitivity analysis using (1) missing as missing (i.e. no imputation) for dropouts and (2) last observation carried forward (LOCF method) will be performed for the primary endpoint to explore the impact of missing data after a subject drops out. All participants will be included in the intention-to-treat (ITT) analysis, regardless of adherence. In addition, per-protocol (PP) analysis of patients with complete observations will be performed to estimate the effect of missingness or protocol deviations on the statistical analysis.

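### The rule for filling missing data makes no exception for death or for infants too impaired to be tested, so as written it supplies Bayley and BPD values that do not exist or are too favourable

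*Protocol article*

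**What the plan says.** Section {20c} of the protocol article gives one general rule, "Linear regression will be used to fill missing data", and follows it with "All participants will be included in the intention-to-treat (ITT) analysis, regardless of adherence". Its two sensitivity analyses (no imputation, and last observation carried forward) "will be performed for the primary endpoint to explore the impact of missing data after a subject drops out". They therefore do not reach the Bayley scores or BPD.

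Section {20a} adds a second rule: "In cases of missing data, i.e. due to adverse events or dropouts, in follow-up analysis, a weighted average" is to be applied, with account taken of shifts in the sex ratio. Adverse events are thus named as a cause of missing data, next to ordinary dropout.

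The outcomes affected are defined under Outcomes {12}. BPD is "need for oxygen, continuous positive airway pressure (CPAP), or mechanical ventilation at" 36 + 0 weeks, with nothing said about infants who die earlier. The lowest Bayley band, below 70, is labelled "> 2 SD below the mean)—severe impairment", and no rule places an untestable child in it.

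Death closes the list under Exclusion criteria (run together in the text at hand as "daysSepsisDeath"). Infants taken off the intervention stay in the study under Implementation {16c}: "All of these infants will be followed through 36 months as scheduled".

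**The concern.** A missed visit, a death and a child who cannot be tested are three different things. After a missed visit there is a true value that nobody recorded. After death there is no value: an infant who died before 36+0 weeks has no BPD status, and one who died before 12 months has no Bayley score. A survivor who cannot be tested because of severe impairment does have an outcome, and it is a very poor one. A regression built on tested infants tends to predict something ordinary for that child.

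The rule in {20c} treats all three alike. If the arms differ in death or in severe impairment, in either direction, the Bayley and BPD comparisons would understate that difference. Sample size {14} raised the trial from 78 to 91 infants per arm, before loss, specifically for the 12-month cognitive score. Multiple imputation in place of a single fill would repair the variance but not this, because the fault lies in which values are imputed.

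**Working it through.** **1. The plan's own figure.** Sample size {14} gives a difference of 5, SD 12, power 80% and α 0.05; {20a} makes secondary tests two-sided. Then n = 2 × (1.960 + 0.842)² × 12² / 5² = 2 × 7.849 × 144 / 25 = 90.4, which rounds up to the stated 91 per arm. Power at 91 is 80.3%. The 5-point target is a sound yardstick for what follows.

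**2. How much may be filled.** Sample size {14} allows 10% loss; section {18b} projects up to 20% a year. Of 100 infants per arm, roughly 10 to 20 could lack a 12-month score. How many of these would be dead or untestable is not stated anywhere.

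**3. Bayley mean, untestable survivors.** Let e be the excess share of such infants in one arm, s their true score, and 100 the filled value (the planning mean). Hidden difference = e × (100 − s). Assumed scores are s = 69, the top of the below-70 band, and s = 55, a low score.

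| Excess e | s = 69 | s = 55 | Share of 5 points |
|---|---|---|---|
| 1 point | 0.31 | 0.45 | 6–9% |
| 2 points | 0.62 | 0.90 | 12–18% |
| 3 points (5% vs 2%) | 0.93 | 1.35 | 19–27% |
| 5 points | 1.55 | 2.25 | 31–45% |
| 10 points | 3.10 | 4.50 | 62–90% |

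**4. Omission does not help.** Let a share u of an arm be untestable and let the tested mean be m.
- Filled at the arm mean: (1 − u)m + um = m.
- Left out: m.
- Scored at s: m − u(m − s).

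Omission and mean-filling give the same arm mean. Only a floor score or a lowest rank brings the hidden difference back.

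**5. BPD and death.** Assume deaths of 5% and 10% in the two arms and an equal BPD rate b among survivors. Filling the deaths at the survivors' rate shows a difference of 0. For death or BPD, the difference is (0.10 − 0.05) × (1 − b): 4.25 percentage points at b = 15% and 3.0 at b = 40%.

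**6. Scale of the fill.** A linear prediction for a 0/1 outcome is generally neither 0 nor 1. The chi-square and Fisher tests in {20a} need counts.

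**The case against.** The strongest reply is that no sentence says dead infants are imputed. That is true, and a reader should not infer that the sponsor has decided to do so. What is on the page is an unconditional rule with no exception.

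Death under Exclusion criteria might mean that infants who die are removed. It can also be read as covering deaths between consent in the first week and randomisation, which the Intervention description places at 80 ml/kg/day of feeding. If it does mean removal after randomisation, it conflicts with the intention-to-treat statement and discards the worst outcomes instead of counting them.

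The weighted average in {20a} may be only a re-weighting of group means for a changed sex mix, so that no infant is assigned a value. That objection stands: the sentence is ambiguous, is confined to follow-up analysis, and cannot carry the point. It still does not separate death or untestability from dropout.

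A regression using severity predictors such as IVH or PVL could give lower values than 100. No predictors are named, so this can be neither relied on nor ruled out.

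IVH, PVL, NEC and sepsis are compared between arms, and adverse events up to discharge are reported, so it goes too far to say that the trial would see nothing. But mortality is not a listed outcome, adverse-event collection stops at discharge, and the per-protocol analysis of complete observations leaves these infants out.

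Finally, an article may leave imputation detail to an analysis plan. Here, however, it states a general rule, and that rule gives a wrong result when followed.

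**Conclusion.** The point holds in a limited form. Followed literally, {20c} produces BPD and Bayley values for infants who died, tends to give ordinary scores to survivors too impaired to be tested, and yields unusable fractions for BPD. No planned sensitivity analysis of those outcomes would test this.

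Its size cannot be derived from the documents. The range of 0.31 to 0.45 Bayley points per percentage point of imbalance assumes a fill of about 100 and true scores of 69 or 55, and it concerns untestable survivors only. The 1.35 points (27% of the target) for a 5% vs 2% split is an illustration; it should not be read as an expected bias. The BPD figures rest equally on assumed death rates.

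The outcomes are secondary, but one of them set the sample size and the correction is cheap, so the text should be changed.

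**What to change.** 1. State in {20a} and {20c} that no outcome value is filled after death. Reconcile the Death entry under Exclusion criteria with the intention-to-treat statement, so that deaths after randomisation stay in the randomised set and are reported by arm. Say whether the weighted average in {20a} re-weights group means or assigns values.
2. Classify survivors untestable because of severe impairment as below 70. In the continuous Bayley comparison give them the scale's floor score or the lowest rank; the Mann-Whitney test is already in {20a}. Neither regression fill nor omission will do.
3. Add two supportive analyses with components shown: death or cognitive composite below 70 at 12 months, and death before 36+0 weeks or BPD.
4. Restrict imputation to living, testable infants who missed the assessment, with a model suited to the outcome type.

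**Cost.** Analysis wording, plus vital status and a reason-not-tested field in the e-CRF. Composites mix outcomes, and the Bayley comparison remains conditional on survival.

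A floor score also widens the SD. If 12 describes tested infants and a share u in each arm is set to 55, the variance is (1 − u) × 144 + u(1 − u) × 45². That gives an SD of 13.4 at u = 2% and 15.3 at u = 5%. Power for 5 points with 91 per arm, from Φ(5 / (SD × √(2/91)) − 1.96), is then about 71% and 60%. The lowest-rank option is less exposed, because an extreme score can move an infant only to the bottom of the ranking. The choice should be fixed before unblinding.

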### Outcomes {12}

#### Primary outcome

Weight gain velocity (grammes per week) will be measured daily starting from the day infants regain their birth weight up to 4 weeks, then weekly until discharge. Length and head circumference will be measured in centimetres weekly until discharge.

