### Sample size {14}

The sample size required to compare two means in two-sided equality test was estimated based on results from a prior double blind, randomized clinical trial, investigating the effect of TG vs SF of breast milk on the changes of anthropometric parameters and body composition in preterm children [23, 24]. It was determined that a mean difference of weight gain 1.9 g/kg/day between groups would be clinically important and feasible during intervention.

The following assumptions were made for the calculation: type I error (α) 5%, power 80%, equal sample sizes in both groups, the mean weight gain in the standard fortification group 19.3 g/kg/day, and the mean weight gain in the target fortification group 21.2 g/kg/day. To account for the higher uncertainty in measured weight gain due to differences between the studied and the quoted trial population, standard deviation value taken from the prior trial was increased by 50% to 3.75.

An estimated minimum size of each group is 68. Accounting for a presumed 20% attrition rate, due to potential dropouts, deviations from the protocol, and loss to follow-up, a minimum sample size required was estimated at 156 infants or 78 infants per treatment arm.

However, in order to detect a difference of 5 points in cognitive score of Bayley-III (secondary outcome) at 12 months of age (mean of 100 points, standard deviation (SD) 12) between the study groups with a power of 80% and α = 0.05, we have decided to increase the sample to 91 infants in each study group.

In summary, allowing for 10% of loss to follow-up, the target number of 200 premature infants will be recruited.

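### One of the two sensitivity analyses for the primary growth endpoint carries the last observation forward, an implausible assumption for a growing infant that makes a poor robustness check

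*Protocol article*

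**What the plan says.** All references are to the protocol article.

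- **Missing data {20c}.** The main rule is "Linear regression will be used to fill missing data". Two sensitivity analyses for the primary endpoint follow. The first leaves dropouts unimputed. In the second, "last observation carried forward (LOCF method) will be performed for the primary endpoint to explore the impact of missing data". A further check is named: "per-protocol (PP) analysis of patients with complete observations will be performed to estimate the effect of missingness or protocol deviations".
- **Statistical methods {20a}.** A different rule is given for missing data in follow-up analysis: "a weighted average taking account of changes in the gender ratio will be applied". This is not carrying forward either.
- **Outcomes {12}.** The entry for the primary endpoint reads: "Weight gain velocity (grammes per week) will be measured daily starting from the day infants regain their birth weight up to 4 weeks, then weekly". Weighing ends when the infant leaves hospital. The unit here is grams per week.
- **Sample size {14}.** The design effect is in another unit: 19.3 against 21.2 g/kg/day, a difference of 1.9, with SD 3.75. An allowance is described as "Accounting for a presumed 20% attrition rate, due to potential dropouts, deviations from the protocol, and loss to follow-up". The final target of 200 uses a 10% loss allowance.
- **Implementation {16c} and retention {18b}.** Infants who stop the intervention stay in the study and keep the same assessment schedule. Withdrawal from the study is possible at any time.

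**The concern.** Carrying the last observation forward assumes that the outcome stays where it was when last seen. The protocol's own figures have these infants gaining roughly 2% of body weight a day, so the assumption fails for weight and for weekly gain in grams.

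A sensitivity analysis should vary the assumption about unobserved growth over a believable range. This one departs from the main analysis in a direction set by how many infants leave each arm and when. If it disagrees with the main result, a reader cannot tell a fragile finding from an artefact. If it agrees, little has been learned. The other listed approaches (regression fill, no imputation, complete observations) all lean on data being missing at random or on something stronger, so the plan has no credible check of departures from that.

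**Working it through.** The plan gives no figure for the effect of this rule, so there is nothing of its own to reproduce.

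**Inputs from Sample size {14}:** means m of 19.3 (standard) and 21.2 (targeted) g/kg/day; SD s = 3.75. The planned 200 infants give 100 per arm.

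**Assumptions not in the document:** the last weight is carried; velocity is taken over the full window; dropout time is uniform over the window and unrelated to the infant's velocity; dropout rates d are as shown.

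**Reading 1: last weight held.** An infant lost at fraction f of the window scores f times its velocity. With f uniform, the mean of f is 0.5, so the scored arm mean is m × (1 − d/2).

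- Equal 20%: 21.2 × 0.90 − 19.3 × 0.90 = 19.08 − 17.37 = 1.71. Under the null the difference stays 0.
- 10% standard, 20% targeted: 21.2 × 0.90 − 19.3 × 0.95 = 19.08 − 18.335 = 0.745. Under the null: 19.3 × (0.90 − 0.95) = −0.965.
- 20% standard, 10% targeted: 21.2 × 0.95 − 19.3 × 0.90 = 20.14 − 17.37 = 2.77. Under the null: +0.965.
- 3% standard, 5% targeted: 21.2 × 0.975 − 19.3 × 0.985 = 20.67 − 19.01 = 1.66. Under the null: 19.3 × (0.975 − 0.985) = −0.193.

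Timing matters. For 10% against 20% with every dropout at one quarter of the window, the arm mean is m × (1 − 0.75d): 21.2 × 0.85 − 19.3 × 0.925 = 0.17, and −1.45 under the null. At three quarters it is m × (1 − 0.25d): 21.2 × 0.95 − 19.3 × 0.975 = 1.32, and −0.48 under the null.

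False rejection under the null, 10% against 20%, uniform timing: the scored variance is (m² + s²)(1 − 2d/3) − [m(1 − d/2)]², with m² + s² = 372.49 + 14.06 = 386.55.

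- d = 0.10: 360.78 − 336.17 = 24.6.
- d = 0.20: 335.01 − 301.72 = 33.3.
- Standard error at 100 per arm: √((24.6 + 33.3)/100) = 0.76. The shift is 0.965/0.76 = 1.27 standard errors, so a two-sided 5% test rejects about 25% of the time. For 3% against 5% the same calculation gives about 6%.

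**Reading 2: last weekly gain in grams held** (the unit in Outcomes {12}). Take an assumed 1.0 kg infant growing continuously at 19.3 g/kg/day. Weekly growth is a factor exp(7 × 0.0193) = 1.145, and the gains in weeks 1 to 4 are 145, 166, 190 and 217 g (mean 179). Carrying week 1 forward scores 145, and 145/179 = 0.81, so the infant is scored 19% low.

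**Reading 3: velocity in g/kg/day held** (the unit in Sample size {14}). If relative growth is constant, the carried value equals the true one and there is no bias.

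Section {20c} does not say which of the three applies.

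**The case against.** The strongest reply is that little depends on this analysis. It is one of two named sensitivity analyses, a per-protocol analysis sits beside them, and the headline result uses regression imputation. The quantity carried may be set out in an analysis plan that is not shown, and one possible choice is harmless. The primary endpoint is measured in hospital, where few weights may be missing. All of this stands, and it limits the point to the quality of a secondary check.

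Four stronger readings are tempting, and the documents do not support them.

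- *The primary result is biased.* It is not: carrying forward is not the main method.
- *Every dropout is scored too low.* This holds for readings 1 and 2, not for reading 3.
- *The discontinuation criteria in {11b} (poor tolerance, NEC, sepsis) drive unequal dropout.* Those criteria stop the intervention, not the weighing. Under {16c} and {18b} these infants stay on schedule, so only infants whose measurements cease are affected. Nothing in the article shows that this will differ by arm.
- *Power collapses from about 93% to about 48%.* That contrast puts 20% dropout on 91 per arm, which is the number before the final loss allowance. The 20% in {14} also covers protocol deviations and is not a rate of missing inpatient weights. Part of the fall is plain data loss: analysing only the 73 completers per arm (0.8 × 91) already brings power to about 86%.

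The reply does not rescue the choice. Harmlessness requires a particular quantity, a particular unit and constant relative growth, while the article's own outcome section uses grams per week.

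**Conclusion.** The point holds in limited form. A named sensitivity analysis for the primary endpoint rests on an assumption that is implausible for growth under two of its three readings, and {20c} leaves the reading open. With the last weight held, equal dropout only dilutes a true effect (1.9 to 1.71 at 20%). A false difference needs unequal dropout rate or timing: about −0.97 g/kg/day at 10% against 20%, roughly half the design difference, and only −0.19 at 3% against 5%. Its sign follows whichever arm loses more infants, or loses them earlier. These sizes are illustrative, because dropout rates and timing are assumed. What is at stake is a misleading robustness check, and it is worth correcting because the correction is cheap.

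**What to change.** In {20c}, delete last observation carried forward and put two analyses of the primary endpoint in its place:

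1. A repeated-measures mixed model on log weight, with random intercept and slope, using every weight observed before dropout.
2. A delta-adjusted (tipping-point) multiple imputation that lowers velocity after dropout over a range stated in advance, separately in each arm, and reports where the conclusion changes.

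The first still assumes missing at random; the second tests departures from it. Other models could serve, provided they use the observed weights and vary the assumption about unobserved growth. Keep the no-imputation analysis already listed. Use one velocity unit in Outcomes {12} and Sample size {14}.

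The cost is revised wording and slightly more programming. The daily and weekly weights are already collected, so no new data are needed.

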#### Criteria for discontinuing or modifying allocated interventions {11b}

The following are the criteria for discontinuing allocated intervention:
SepsisNECWithdrawal of parental/guardian consentPoor feeding tolerance defined as increasing abdominal distension > 2 cm between inter-observer measurement and/or regurgitations after feeding > 3 feeds per day

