#### Relevant concomitant care permitted or prohibited during the trial {11d}

Participants should continue to receive standard neonatal care. Interventions aimed at improving weight gain such as increased daily intake (> 160–170 ml/kg/day) or increased dosing of vitamin D (> 1000 IU/l) or prescription of milk formula will be forbidden.

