#### Plans to promote participant retention and complete follow-up {18b}

All randomized infants who are prematurely discontinued from study drug will be considered *off study drug/on study*. They will follow the same participant timetable as those infants who continue study treatment. All of these infants will be followed through 36 months as scheduled.

Once an infant is enrolled or randomized, the study site will make every reasonable effort to follow the infant for the entire study period. It is projected that the rate of loss to follow-up on an annual basis will be at most 20%. Each study site staff will develop and implement local standard operating procedures to achieve this level of follow-up.

Participants may withdraw from the study for any reason at any time. The investigator also may withdraw participants from the study in order to protect their safety.

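### The per-protocol analysis is selected on complete data with no stated adherence rule, so it cannot separate protocol deviations from missingness

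*Protocol article*

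**What the plan says.** Section {20c} of the protocol article first sets the main analysis: "All participants will be included in the intention-to-treat (ITT) analysis, regardless of adherence". It then adds that a "per-protocol (PP) analysis of patients with complete observations will be performed to estimate the effect of missingness or protocol deviations". It also lists two sensitivity analyses for the primary endpoint. One leaves the data of dropouts unimputed and the other carries the last observation forward.

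The per-protocol set appears in one other place, section {20a}: "Baseline characteristics will be presented for all included neonates in intention-to-treat and per-protocol analysis sets, by treatment group". That sentence uses the set but does not say who belongs to it.

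Three other parts of the article bear on membership:
- Section {11b}, introduced by "The following are the criteria for discontinuing allocated intervention", lists sepsis, NEC, withdrawal of consent and poor feeding tolerance.
- Section {16c} says that infants taken off the intervention "will follow the same schedule of events as those infants who continue study treatment". Section {18b} repeats this: "They will follow the same participant timetable as those infants who continue study treatment".
- Section {11d} prohibits certain care during the trial. Its list ends with "or prescription of milk formula will be forbidden".

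**The concern.** A per-protocol set is meant to show what the treatment difference looks like among infants who were treated as planned. The attribute that matters is adherence. The attribute that section {20c} states is whether the data are complete. The two are different here, because the protocol deliberately continues to measure infants who have come off the allocated fortification.

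The stated purpose adds to the difficulty. One analysis is to estimate the effect of missing data or of deviations. If its result differs from ITT, the reader cannot tell which of the two is responsible. If it agrees, the reader may conclude that deviations do not matter, although infants with deviations may never have been removed.

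**Working it through.** No figure in the plan depends on this definition, so the main check is to apply the stated rule to cases that the protocol itself makes possible.

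**Step 1: three infants under two readings.** The literal reading uses complete data as the only criterion. The generous reading requires adherence as well as complete data.

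| Infant | Source of the case | Literal reading | Generous reading |
|---|---|---|---|
| A: targeted arm, stopped on day 2 of the step-up for poor tolerance, all weights recorded | {11a}, {11b}, {16c}, {18b} | In | Unclear: the stop is protocol-specified |
| B: given formula, all weights recorded | {11d} | In | Out |
| C: on allocated fortification throughout, one weekly measurement missed | {12} | Out, if one gap counts as incomplete | Out, on the same condition |

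The literal reading keeps A and B and drops C. The generous reading corrects B, leaves A undecided and still drops C. Infants whose parents withdraw consent may leave follow-up altogether. The other three reasons in {11b} leave the infant on the schedule.

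**Step 2: how mixed the set could be.** The protocol gives no separate rates for stopping or for data gaps, so both are assumed. Take 100 infants in an arm. Let q be the share off fortification but fully measured, and m the share of adherent infants with a gap.

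- Set size on the literal reading: 100q + 100(1 − q)(1 − m)
- Non-adherent share: 100q divided by that size
- Adherent infants excluded: 100(1 − q)m

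With q = m = 10%, the size is 10 + 90 × 0.9 = 91. The non-adherent share is 10/91 = 11%, and 90 × 0.1 = 9 adherent infants are excluded. With q and m each between 5% and 20%:
- the non-adherent share runs from 5/95.25 = 5% to 20/84 = 24%;
- adherent infants excluded run from 80 × 0.05 = 4 to 95 × 0.20 = 19.

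**Step 3: what this does to the contrast.** The input is the planned difference of 1.9 g/kg/day from section {14}. Assume that a share q of the targeted arm stops, keeps none of the benefit and is fully measured, and that no other infant has a gap. The expected difference is then 1.9 × (1 − q):
- q = 10%: 1.9 × 0.90 = 1.71
- q = 20%: 1.9 × 0.80 = 1.52

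On the literal reading, ITT and the per-protocol analysis then contain the same infants and give the same diluted figure.

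**Step 4: consistency with the sample size.** Section {14} counts protocol deviations, with dropouts and loss to follow-up, in its 20% attrition. It therefore plans as though infants with deviations leave the analysis. The stated criterion in {20c} does not remove them.

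**The case against.** The strongest reply is that completeness is a qualifier and not a definition. The sentence follows directly on an ITT statement that disregards adherence, and the term per-protocol carries its ordinary meaning. On that view the set holds infants treated as planned who also have complete data, and the detailed rules sit in an analysis plan that is not shown. This is fair, and it means the documents do not prove that adherence is ignored. A bare absence of adherence rules from an article would not be a finding. What remains is that the one criterion actually stated discards adherent infants with gaps and puts missingness and deviations into a single comparison. That holds on either reading.

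Three further objections succeed in part:
- A reader might infer that the per-protocol analysis simply duplicates the unimputed sensitivity analysis. On the literal reading the overlap is large but not total, because the latter is stated for dropouts and the primary endpoint only.
- A reader might infer that completeness extends to the 3.5-year visit and so removes a large part of the trial from an in-hospital comparison. Nothing in the article ties completeness for the growth outcome to later visits, so no such loss can be claimed.
- Removing every infant who stopped under {11b} would also select on events after randomisation. NEC, sepsis and feeding tolerance are themselves secondary outcomes. An adherence-based set is therefore not free of bias either.

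**Conclusion.** The point holds in a limited form. As written, the rule can admit non-adherent infants and exclude adherent ones. Even with adherence implied, it cannot separate the effect of deviations from that of missing data. Agreement between ITT and this analysis would not be evidence of robustness to deviations.

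The ITT analysis of all participants is untouched, and no stated figure changes. The 1.7 and 1.5 g/kg/day values, and the 5–24% non-adherent share, are illustrations under assumed rates and not forecasts. The ITT dilution occurs however the per-protocol set is defined; the defect is that this set may fail to reveal it.

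The change is worth making before unblinding. Section {20a} names a noninferiority test for the primary outcome, although section {8} describes a superiority trial. That conflict is a separate matter, but if the noninferiority test were kept, a sound per-protocol set would matter more, since non-adherence tends to draw the arms together.

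**What to change.** Replace the per-protocol sentence in {20c} with a definition based on adherence:
- The infant met the inclusion and exclusion criteria in {10} as they stood at randomisation.
- The infant received the allocated fortification during the primary-outcome window.
- The infant received none of the care prohibited in {11d} during that window.
- Membership is fixed blind to outcome and does not depend on complete data.

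The window must be named, because the Abstract, {12} and {18a} give different end points for the growth measurement. State whether discontinuations specified in {11b} lead to exclusion. Describe the analysis as supportive, since those stops occur after randomisation and overlap with outcomes.

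Report the complete-observation analysis separately, as a complete-case sensitivity analysis alongside the other missing-data analyses, and do not call it per-protocol.

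The cost is wording and a blinded review of adherence. No additional infants or visits are needed and no clinical rule changes. The per-protocol set may become somewhat smaller.
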